### Pilot study results

We have completed an initial pilot study that has informed the study design allowing an estimate of appropriate sample size and likely recruitment, alongside an evaluation of outcome measures. The results of this study have been published by the European Journal of Obstetrics & Gynaecology and Reproductive Biology. [16] The pilot study represented a single centre randomised controlled trial of oxytocin 5 IU and placebo infusion versus oxytocin 5 IU bolus and oxytocin 30 IU infusion. We chose a 30 IU infusion as this was the approach recommended in the NICE Guideline on induction of labour. We have changed the study design to a 40 IU infusion reflecting preferred practice within the national survey and the recommendation of emergency obstetrics training courses (ALSO). The pilot results therefore reflect a slightly lower oxytocin concentration than is planned for the multi-centre study.

### Feasibility

The pilot study was conducted over an eight month period in a unit with 3400 deliveries a year. We received approval from the Edinburgh multi-centre research ethics committee (MREC) and approval of the UK MHRA in keeping with the requirements of the EU directive on Clinical Trials. The obstetricians, anaesthetists, midwives, theatre staff and hospital pharmacist were very supportive. We received a high level of support from women undergoing caesarean section, the majority of who were happy to participate in the trial. There were no serious unexpected adverse events. The recruitment is summarised in the Consort flow chart. (Figure 1)

**Figure 1 F1:**
[figure not shown]
**Oxytocin at Caesarean Section Pilot Study – CONSORT Flowchart**.

### Sample size

We estimate from the pilot study that 5–10% of study participants will have an estimated blood loss of > 1000 ml. The rate is around 15% for the calculated estimate (EBL_calc_) and this is more likely to be an accurate reflection of actual blood loss. We found relative reductions of between 20–50% in the outcome measures on comparing infusion and placebo in the pilot study, but with wide 95% confidence intervals around these estimates. It is also possible that a pilot study will over or under estimate differences and we have therefore chosen conservative effect estimates for this multi-centre study.

With 1000 patients per group for analysis, the study will have 80% power at the 5% two-sided alpha level, to detect differences in the proportion of patients with clinician estimated blood loss >1000 ml of 15% vs. 10.7%, or 10% vs. 6.4%, equivalent to odds ratios of 0.62 and 0.68 respectively.

For the co-primary outcome of calculated blood loss, and estimated incidence in the control group of 14%, n = 1000 per group has 80% power to detect a difference 4.2%, equivalent to odds ratio of 0.67.

Based on the hospital statistics in the Dublin Maternity units for 2004 we estimate that there will be approximately 2500 elective caesarean sections at term each year between the five centres. Over the course of 30 months we would aim to recruit 2112 patients representing almost 34% of the available population (2112/6250) – this conservative estimate takes account of eligibility criteria and non-English speaking women. The sample size is slightly inflated from 2000 to allow for missing outcome data (full blood count not taken at the correct time or blood loss not measured).

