### Primary outcomes

- to compare the incidence of major obstetric haemorrhage (≥ 1000 ml) following oxytocin bolus compared with oxytocin bolus and infusion

- to compare the need for an additional uterotonic agent between the two groups

Major obstetric haemorrhage will be defined by:

- measured blood loss as calculated from pre and post-operative haematocrit (see below)

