### Secondary outcomes

- to compare the estimated mean operative blood loss between the two groups (as measured by theatre staff)

- to compare early lochial loss following oxytocin bolus compared with oxytocin bolus and infusion

- to compare the objective change in haemoglobin and haematocrit before and 48 hours after delivery between the two groups

- to compare the incidence of severe anaemia (Hb fall ≥ 20%) 48 hours after delivery between the two groups (or patient transfused).

- to compare the need for blood transfusion and/or blood products

- to compare the incidence of side effects (vomiting, hypotension)

- to compare the postnatal length of stay in theatre/recovery and in the hospital

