### Outcome measures

The primary outcome measures are major obstetric haemorrhage (estimated blood loss ≥ 1000 ml) and use of an additional uterotonic agent. Estimated blood loss of ≥1000 ml has been chosen to reflect major obstetric haemorrhage and it is widely accepted that clinicians underestimate rather than overestimate blood loss. This estimate will be based on the difference between pre-operative and post-operative haematocrit (EBL_calc _– Calculated estimated blood loss). [14]

The estimate is calculated as follows:

Where EBV estimated blood volume = Booking weight in kg × 85

Secondary outcomes include mean estimated blood loss (as measured by theatre staff), change in haemoglobin and haematocrit, significant anaemia (Hb fall = 20%) 48 hours after delivery, need for blood transfusion, side effects (including vomiting and hypotension) and length of postnatal stay in theatre/recovery and in hospital. Hypotension will be defined as a fall in blood pressure of more than 30% below the pre-operative blood pressure and/or use of ephedrine.

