### Statistical analysis

Data analysis and reporting will proceed according to CONSORT guidelines for randomised controlled trials, and will be conducted blinded to group status by the trial statistician and researcher. The first stage of analysis will be to use descriptive statistics to describe recruited individuals in relation to those eligible, and to investigate comparability of the trial arms at baseline. The primary analyses will involve intention-to-treat comparisons between the two groups for the primary outcomes, with transformation as appropriate after examination of distributions, and adjusted for stratification variables. Secondary analyses will investigate the effects of further adjustment for any variables displaying marked imbalance between the arms at baseline. Secondary outcomes will be analysed in a similar way. All analyses will use appropriate (that is, logistic or linear) regression models, with results presented as point estimates (odds ratios or difference in means), 95% confidence intervals and p values. Further secondary analyses will involve planned subgroup analyses and will use multivariable regression models with appropriate interaction terms to ascertain any differential effects in relation to repeat caesarean section, choice of anaesthetic, and operator experience.

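### Two primary outcomes are declared with no success rule; the sample size spends the full 5% on blood loss and gives no power for the uterotonic outcome

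*Protocol article*

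**What the plan says.** The protocol article describes its primary outcomes differently from section to section.

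- **Abstract, Methods and design:** one main outcome, major haemorrhage, with 80% power at two-sided 5% for a 36% relative change.
- **Primary outcomes (under Aims and objectives):** two items. The first is the incidence of major haemorrhage, defined by "measured blood loss as calculated from pre and post-operative haematocrit". The second is "to compare the need for an additional uterotonic agent between the two groups".
- **Outcome measures:** the same two. "The primary outcome measures are major obstetric haemorrhage (estimated blood loss ≥ 1000 ml) and use of an additional uterotonic agent".
- **Secondary outcomes:** the theatre-staff estimate of blood loss appears here, as a mean: "to compare the estimated mean operative blood loss between the two groups (as measured by theatre staff".
- **Sample size:** "With 1000 patients per group for analysis", "the study will have 80% power at the 5% two-sided alpha level" for clinician-estimated loss above 1000 ml (15% vs 10.7%, or 10% vs 6.4%). A second calculation begins "For the co-primary outcome of calculated blood loss, and estimated incidence in the control group of 14" per cent and gives 80% power for a difference of 4.2 points. Additional uterotonic use is not mentioned.
- **Statistical analysis:** "The primary analyses will involve intention-to-treat comparisons between the two groups for the primary outcomes", reported as estimates with 95% confidence intervals and p values. No order of testing, division of alpha or either/both rule is given.

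**The concern.** With two primary outcomes, the trial's error rate and power depend on what counts as success. The protocol fixes 1000 patients per group at the full two-sided 5%, but it does not say whether one significant primary is enough, whether both are needed, or whether one comes first.

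The outcomes it sizes are also not the outcomes it declares. Both calculations concern blood loss. One uses a measure that is otherwise only a secondary outcome, and the second declared primary has no calculation.

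The practical risk is an asymmetric result. Under Intervention, the obstetrician or anaesthetist may give a further uterotonic if the uterus stays atonic, so that outcome depends partly on clinical judgement. If it were significant and haemorrhage were not, nothing in the text would stop it being reported as success on a primary outcome, at a trial-wide error rate above the stated 5%.

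**Working it through.** **1. Inputs.** From Sample size: n = 1000 per group, two-sided 5%, 80% power, and the pairs 15% vs 10.7%, 10% vs 6.4% and 14% vs 9.8% (14 − 4.2). Alpha is not restated for the third pair and is taken as 5% two-sided. The correlation ρ between the two primary test statistics is not in the document; 0 to 0.9 is assumed.

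**2. Reproducing the stated power.** Normal approximation for two proportions:

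power = Φ{(d − z·SE₀)/SE₁}, where SE₀ uses the pooled proportion and SE₁ the separate proportions.

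For 14% vs 9.8%: d = 0.042; SE₀ = √(2 × 0.119 × 0.881/1000) = 0.01448; SE₁ = √((0.14 × 0.86 + 0.098 × 0.902)/1000) = 0.01445. Power = Φ{(0.042 − 1.96 × 0.01448)/0.01445} = Φ(0.94) = 82.7%.

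With the continuity correction, n is replaced by 1000 × (1 − 1/(1000 × 0.042))² = 953, and power is 80.9%.

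| Pair | Power, uncorrected | Power, corrected |
|---|---|---|
| 15% vs 10.7% | 82.0% | 80.2% |
| 10% vs 6.4% | 83.6% | 81.4% |
| 14% vs 9.8% | 82.7% | 80.9% |

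The stated 80% is therefore sound for each blood-loss comparison taken alone at 5%.

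**3. Which outcome the Abstract's figure describes.** The relative reductions are 1 − 10.7/15 = 28.7%, 1 − 6.4/10 = 36% and 1 − 9.8/14 = 30%. The Abstract's 36% matches the 10% vs 6.4% pair, which is clinician-estimated loss, not the calculated loss that defines the primary outcome.

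**4. If either primary may carry the claim.** Familywise error = 1 − P(|Z₁| < 1.96 and |Z₂| < 1.96). With ρ = 0 this is 1 − 0.95² = 9.75%. Other values come from the bivariate normal (table below).

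**5. If both must be significant.** Testing each at 5% needs no adjustment. Power for both cannot exceed the power for haemorrhage, nominally 80%, and falls below it unless the uterotonic comparison is almost certain to be significant. No power for that comparison is given, so the joint figure cannot be computed. As an illustration only, suppose it also had 80%. Each statistic then has mean 1.96 + 0.84 = 2.80, and joint power = P(Z₁ > 1.96 and Z₂ > 1.96), which is 0.8 × 0.8 = 64% at ρ = 0.

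| ρ (assumed) | Familywise error, either rule | Joint power, both rule (illustrative) |
|---|---|---|
| 0 | 9.75% | 64.0% |
| 0.5 | 9.1% | 68.7% |
| 0.7 | 8.3% | 71.3% |
| 0.9 | 7.0% | 75.0% |

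**6. If alpha is shared.** At 2.5% (z = 2.241), power for 14% vs 9.8% is Φ{(0.042 − 2.241 × 0.01448)/0.01445} = Φ(0.66) = 74.6% uncorrected and 72.3% corrected. The intervention-group rate detectable with 80% power is 9.56% uncorrected and 9.47% corrected, a difference of 4.4 to 4.5 points instead of 4.2.

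**The case against.** The strongest reply is that only a condensed article is at hand and a testing rule may sit in an analysis plan that is not shown. That is fair as far as silence in the Statistical analysis section goes. It does not cover the sample size, which is fixed here and depends on the rule: an unseen plan that split alpha would no longer match the 80% stated for 14% vs 9.8%. Nor does it explain why the sections of this article disagree on which outcomes are primary.

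A second reply is that the Abstract and the hypothesis in the Background point to haemorrhage as the lead. The hypothesis names major haemorrhage and anaemia and does not mention uterotonic use. This stands in part. Read with haemorrhage first, 5% and 80% both hold for that outcome, so it would be wrong to infer that no reading delivers the stated pair. But the body of the protocol states no such order and lists the two primaries on equal terms.

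Third, the two outcomes are plausibly positively correlated, since a further uterotonic is given for atony. That also stands: 9.75% and 64% are the values under independence, the least favourable if the correlation is not negative.

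Finally, a reader might infer that each declared primary was powered at 80% and that the trial's joint power is therefore about 64%. The document does not support this. The two powered measures are both blood loss, and nothing is given for the uterotonic outcome.

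**Conclusion.** The point holds in this form: two primary outcomes are declared with no success rule, the full two-sided 5% is spent on blood loss, and the second declared primary has no stated power.

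If either outcome may be claimed, the familywise error lies between 7.0% and 9.75% for correlations from 0.9 down to 0. If both are required, the error rate is not inflated; overall power is limited by the haemorrhage comparison and otherwise unknown. The 64% to 75% range is conditional on an 80% power for the uterotonic outcome that the document does not claim. All these figures rest on an assumed correlation.

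The individual blood-loss calculations are correct for power. The plan should be amended, but the sample size need not change.

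**What to change.** **Preferred: a fixed sequence.** In Statistical analysis, name calculated blood loss of at least 1000 ml as the first primary outcome, tested at two-sided 5%. Test additional uterotonic use at two-sided 5% only if the first test is significant. This holds the familywise error at 5% and leaves the 14% vs 9.8% calculation intact (about 81% power with continuity correction).

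**Align the other sections.** Give the same order in the Abstract, Primary outcomes and Outcome measures. In Sample size, say that the 80% power applies to calculated blood loss and not to the uterotonic outcome, and present the clinician-estimated figures as supporting information. If the Abstract is to describe calculated loss, its relative change becomes 30% (4.2/14) instead of 36%.

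**Alternative: Holm.** If the sponsor wants either outcome to be able to carry the claim, use Holm at a familywise two-sided 5%. Restate the 80% detectable difference at the 2.5% step as about 4.4 to 4.5 points from 14%, since power for 14% vs 9.8% at that step is 72% to 75%.

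**Cost.** Wording changes in five places and no extra patients. Under the fixed sequence, a significant uterotonic result without a significant haemorrhage result could not be claimed as primary success. Under Holm, the detectable difference is about 0.2 to 0.3 points less favourable.

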### Timetable

Total 36 months: Commencing 01.09.07 – Estimated completion date 31.03.10

Month 0–2: Validate datasets; Raise study awareness; Finalise recruitment procedures

Month 3–33: Recruit participants and complete documentation and follow-up

Month 34–36: Analysis; Final report; Peer-review publications; Presentations.

### Governance issues

#### Ethical Committee Permission

Full ethical approval has previously been received for an eight- month local pilot study designed to develop the trial documentation and to test early feasibility issues.

05/MRE10/20 Approval date 16.03.05 MREC for Scotland

Ethical committee approval (Clinical Trials approved Committee) from the Coombe Women's Hospital, the National Maternity Hospital and the Rotunda Hospital, and approval of the Irish Medicines Board have been granted for this study.

IMB Application date 12.03.07 Approval date 27.04.07

Clinical trials approved committee Approval date 29.11.07

### Data management

Data will be collected in duplicate on a case report form (CRF) at the time of recruitment by a trained researcher. The researcher will also be responsible for ensuring that the details of the delivery are recorded and the blood loss measured. The inpatient notes will be marked so that they can easily be recovered following discharge from hospital. After discharge the CRF will be collected by the local co-ordinator and the completeness of the data checked against the woman's notes. Any errors will be followed up at this time. The data will be entered into a computer database (password protected) at the Coombe Women's Hospital.

### Trial Management Group (TMG)

This group will be in charge of the everyday running of the trial. The full group will meet 4-monthly and as required. Day-to-day decision making will be by [name], [name] and the trial researcher.

### Trial Steering Committee

A trial steering committee will be set up which will have overall supervision of the trial. It will meet prior to commencement of the trial and then at least 6 monthly until completion. A meeting of the TSC will be held within a month of every DMEC meeting to consider their recommendations. An independent Chair will be sought for the TSC.

### Data monitoring and Ethics Committee (DMEC)

An independent safety and data monitoring committee will also be formed. They will meet yearly to examine recruitment figures, baseline data, retention and adverse events. The DMEC will not undertake any formal interim analyses for either safety or effectiveness and therefore there are no formal stopping rules. There is no evidence of adverse reactions associated with oxytocin infusion. Although adverse reactions have been shown to be associated with the 5 IU oxytocin bolus, all trial participants will receive a bolus, and thus we do not anticipate any differences in rates of adverse events between the groups. However all adverse events will be reported to the DMEC who will report these data to the Trial Steering Committee. Additionally, in the event of a postpartum haemorrhage, clinicians are permitted to discontinue the trial infusion and commence a known 40 IU oxytocin infusion.

### Safety considerations

Serious or unexpected serious adverse reactions (SUSARs) will be recorded and reported using the IMB approved SUSAR form. SUSARs include maternal death, surgery (other than caesarean section) in the 2 weeks following randomisation, transfusion of over 4 units of blood, admission to intensive care unit or suspected drug reactions. In the event of a SUSAR the form will be completed by the local trial co-ordinator and faxed to the trial co-ordinating centre at the Coombe Women's Hospital within 72 hours. From there the copies of the form will be sent to the trial statistician for unblinding and the chair of the Data Monitoring and Ethics Committee (DMEC). The IMB, the trial sponsor and the Chair of the MREC will also be informed by the DMEC Chair if considered appropriate.

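### The SUSAR definition has no expectedness test and takes in severe events with no suspected link to the drug, and every such report goes for unblinding

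*Protocol article*

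**What the plan says.** The Safety considerations section opens with the class: "Serious or unexpected serious adverse reactions (SUSARs) will be recorded and reported using the IMB approved SUSAR form". It then says what the class includes: maternal death, surgery other than the caesarean within two weeks of randomisation, and "transfusion of over 4 units of blood, admission to intensive care unit or suspected drug reactions". The procedure follows directly. "In the event of a SUSAR the form will be completed by the local trial co-ordinator" and faxed to the co-ordinating centre within 72 hours. "From there the copies of the form will be sent to the trial statistician for unblinding", and copies also go to the DMEC chair. No step between the list and the unblinding sorts one kind of report from another.

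Four other places bear on this:

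- The DMEC section says of adverse events in general: "However all adverse events will be reported to the DMEC". That sentence mentions neither the SUSAR form nor unblinding. The section also accepts that bolus reactions are known: "Although adverse reactions have been shown to be associated with the 5 IU oxytocin bolus, all trial participants will receive a bolus".
- Secondary outcomes include an aim "to compare the incidence of side effects (vomiting, hypotension"), and also blood transfusion. Outcome measures gives a definition: "Hypotension will be defined as a fall in blood pressure of more than 30% below the pre-operative blood pressure and/or use of ephedrine".
- Statistical analysis says that the trial statistician and the researcher will analyse the data without knowing the groups.
- The Background names transfusion, hysterectomy, intensive care admission and death as consequences of operative morbidity, with haemorrhage listed first.

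**The concern.** A SUSAR category exists to pick out the few events for which breaking the code is justified: serious, not already expected, and suspected to come from the treatment. Here one label covers two different things. One is the grave events of obstetric surgery, whatever their cause. The other is reactions to the drug.

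Two things are at stake. First, codes are broken selectively, for women with the most severe outcomes in a trial whose primary outcome is major haemorrhage, and they are broken by the person who is meant to analyse blind. Second, the DMEC chair receives a single undifferentiated stream, in which an unexpected reaction to trial medication is not set apart from complications of bleeding.

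**Working it through.** No arithmetic applies, because the article gives no rate for any listed event. The check is to apply the three usual tests to the wording.

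**Step 1, the opening phrase.** Its structure is: serious, or (serious and unexpected). The second branch lies inside the first, so the phrase reduces to serious alone and expectedness decides nothing. The protocol does use the right concept elsewhere: the Feasibility section reports that the pilot had no events that were both serious and unexpected.

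**Step 2, the list, item by item.**

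| Listed item | Serious? | Unexpected required? | Suspected drug relation required? | Overlap with trial outcomes |
|---|---|---|---|---|
| Maternal death | By nature | No | Not stated | Background: possible result of severe operative morbidity |
| Further surgery within 2 weeks | In effect | No | Not stated | Background names hysterectomy |
| Transfusion over 4 units | In effect | No | Not stated | Falls within the transfusion outcome; transfused women also count in the severe anaemia outcome |
| Intensive care admission | In effect | No | Not stated | Background: possible result of severe operative morbidity |
| Suspected drug reactions | Only if carried over from the opening phrase | No | Yes | Vomiting and hypotension, on the broadest reading only |

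The expectedness column fails throughout. The causality column fails for four of the five items. The word reactions in the opening phrase might be thought to supply causality for those four. But suspected drug reactions then appears as a separate fifth item, which implies that the first four are not already limited to drug reactions.

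**Step 3, the consequence.** Membership of the list leads to the form, and the form leads to unblinding by the trial statistician. A woman transfused more than 4 units for surgical bleeding therefore has her allocation broken, although nobody need suspect the drug. She also contributes to the transfusion outcome and probably to the haemorrhage outcome. Set beside the Statistical analysis section, this means that the analyst learns the allocation of women with extreme outcomes.

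**Step 4, the last item.** Taken alone, it has no threshold and could reach a non-serious, known side effect. No passage expressly excludes such events from the SUSAR route.

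**The case against.** A reader might infer that ordinary vomiting or hypotension attributed to oxytocin must trigger the form and a code break. With an assumed rate of 5% to 20%, that would be 0.05 × 2112 = 106 to 0.20 × 2112 = 422 code breaks. The documents do not support this. The sentence before the list makes seriousness part of the class, and the neighbouring items are all grave. Vomiting and hypotension are not named in the Safety considerations section. They have their own place as secondary outcomes, and adverse events in general go to the DMEC without mention of unblinding. The rates are invented for illustration, and hypotension under spinal anaesthesia need not be attributed to oxytocin at all. The vomiting reading is a possible literal one that the wording fails to exclude, and no more.

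A second objection is that a journal article condenses the full protocol, so tests of seriousness, expectedness and causality may stand there or on the regulator-approved form. That would answer a complaint that definitions are missing. It does not answer this one, because the article states a rule, lists what falls under it and attaches unblinding to the result.

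A third objection is that the harm to blinding is limited, and this stands in part. Nothing says that the woman, the surgeon, the anaesthetist or ward staff learn the allocation. The exposure named in the article is that of the statistician, with copies of the form going to the DMEC chair. Who should do the unblinding is a separate question; the breadth of the definition decides how often it arises.

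**Conclusion.** The point holds as a defect in the definition. As worded, the class applies no expectedness test, requires no suspected drug relation for four of its five items, and leaves the fifth unqualified. Every report is sent for unblinding, so codes are broken for severe events that overlap the haemorrhage and transfusion outcomes, by a person who is elsewhere said to analyse blind.

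The size cannot be derived, because the documents give no rate for the listed events. The pilot's absence of serious unexpected events does not bound it, since most listed items need not be unexpected. The conclusion assumes only that sites apply the list as written. It does not depend on the broad reading of the last item, nor on any claim that clinical staff are unblinded. The defect is worth correcting and needs only a change of wording.

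**What to change.** Split the Safety considerations text into two categories.

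1. **Serious adverse events:** the four listed grave events and any other serious event, reported within the stated 72 hours without routine unblinding.
2. **SUSARs:** events that are serious, unexpected and suspected to be related to trial medication. Only these are unblinded and sent for expedited report.

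Trial medication should mean the bolus or the infusion. The Intervention section places the 5 IU ampoule in the numbered treatment kits, so a definition limited to the infusion would leave out a serious unexpected reaction to the bolus.

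Qualify suspected drug reactions to match category 2. State that non-serious vomiting and hypotension stay on the case report form as outcomes and go to the DMEC as adverse events, in line with the Secondary outcomes and DMEC sections.

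The cost is revised wording in the protocol and on the form, and a recorded judgement of seriousness, expectedness and causality for each event. In return, outcome events are no longer unblinded without a suspected drug cause, and the DMEC chair can tell suspected drug reactions from complications of bleeding.

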#### Exclusion criteria

Women with placenta praevia, thrombocytopenia, coagulopathies, a previous major obstetric haemorrhage (≥ 1000 ml), known fibroids or receiving anti-coagulant therapy will be excluded as will women who do not understand English and women under the age of 18 years. Other patients may be excluded at the clinician's discretion if a major haemorrhage is anticipated.

Women will be recruited to the trial in the third trimester when initial arrangements are being made for a booked elective caesarean section. The antenatal clinic midwife or research midwife/fellow will approach eligible women and offer information about the study. Women return on the day of surgery and spend a number of hours on the day ward or antenatal ward prior to surgery. At that point the woman's interest in participation in the study will be confirmed, an opportunity to ask additional questions will be provided and informed written consent will be completed. Randomisation will be performed using an automated web-based randomisation system hosted by the Bristol Randomised Trials Collaboration, a UKCRN-registered trials unit. Allocation will be stratified by centre and previous caesarean section (no/yes), and blocked using random permuted blocks of varying size.

The active or placebo infusion will be prepared by the research fellow/midwife. This will be done in the pharmacy department, away from theatre and will be labelled as "Trial drug – Placebo or 40 IU oxytocin". This will ensure blinding of everyone except the research fellow who makes up the infusion, and they will have no role in the management of the patient. Having the research fellow blinded is not possible for two reasons. Firstly, it is not possible to pre-prepare the infusions due to a lack of knowledge of the stability of oxytocin. Secondly, it has not been possible to obtain identically matched placebo ampoules.

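### The trial statistician is to analyse blinded but also unblinds SUSARs, so the blinded analysis is not secured; the exposure lies mainly in secondary analyses

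*Protocol article*

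**What the plan says.** Three sections of the protocol article bear on who knows the allocation.

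- **Statistical analysis.** Data analysis and reporting "will be conducted blinded to group status by the trial statistician and researcher".
- **Safety considerations.** "In the event of a SUSAR the form will be completed by the local trial co-ordinator" and faxed to the co-ordinating centre. "From there the copies of the form will be sent to the trial statistician for unblinding"; copies also go to the DMEC chair. The triggering events are given as a list: "SUSARs include maternal death, surgery (other than caesarean section) in the 2 weeks following randomisation, transfusion of over 4 units of blood", followed by intensive care admission and suspected drug reactions.
- **Exclusion criteria** (the paragraph on preparing the infusion). Of the labelling and off-theatre preparation it says: "This will ensure blinding of everyone except the research fellow who makes up the infusion". The statistician is not named as a further exception.

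The Statistical analysis section also leaves some choices until the data have been seen: transformation after the distributions are examined, and secondary adjustment for baseline variables that turn out markedly imbalanced.

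**The concern.** One role has two duties that conflict as soon as a SUSAR form is processed. The blinded analyst is the person instructed to break the code.

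The women whose allocation would be disclosed are not a random few. The list includes further surgery, transfusion of more than 4 units and intensive care admission, each a possible consequence of severe haemorrhage. Haemorrhage is the subject of a primary objective ("to compare the incidence of major obstetric haemorrhage (≥ 1000 ml) following oxytocin bolus compared with oxytocin bolus and infusion"), and transfusion is a secondary one ("to compare the need for blood transfusion and/or blood products").

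At stake is the article's own safeguard for the analysis. If the analyst knows the arms, choices left open until the data are seen could be made, or be suspected of having been made, with that knowledge. The report could then not claim a blinded analysis without qualification.

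**Working it through.** No stated figure is in question, so the main check compares the text. A short calculation then shows how likely the conflict is to arise.

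**1. Same role?** Statistical analysis and Safety considerations both refer to the trial statistician, with the definite article and no qualifier. No section names an independent statistician, an unblinding officer or a barrier between the two tasks. As written, they fall to one role.

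**2. Is there a filter before unblinding?** The Safety considerations section states none. Suspected drug reactions are one item in the list, separate from death, surgery, transfusion and intensive care admission, so on a plain reading those four qualify as events in themselves. The wording is not tidy, because the term being defined is a serious adverse reaction.

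**3. What does loss of the blind require?** Three things:

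- at least one listed event;
- a dataset that carries a constant code for each of the two groups;
- the statistician's ability to link the unblinded woman to her record.

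If all three hold, one woman is enough to identify both arms. The article does not describe the coding or the linkage, so the second and third are assumptions.

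**4. How likely is at least one event?** The recruitment target is 2112 (Sample size section). The event rate r is not given and is assumed here. Expected events = 2112 × r, and P(at least one) = 1 − (1 − r)^2112.

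| Assumed r | Expected events | P(at least one) |
|---|---|---|
| 0.05% | 2112 × 0.0005 = 1.1 | 65% |
| 0.1% | 2112 × 0.001 = 2.1 | 88% |
| 0.2% | 2112 × 0.002 = 4.2 | 98.5% |
| 0.5% | 2112 × 0.005 = 10.6 | >99.9% |
| 1% | 2112 × 0.01 = 21.1 | >99.9% |

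At the lowest rate shown there is still a 35% chance (100% − 65%) that no form is ever processed and the blind survives.

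**5. Which analyses are open to influence?**

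- *Primary.* Both outcomes are binary: calculated blood loss at or above 1000 ml, and use of an additional uterotonic. A yes/no outcome leaves nothing to transform. The comparison is by intention to treat, with logistic regression adjusted for the stratification variables, which are fixed as centre and previous caesarean section.
- *Secondary.* The Statistical analysis section assigns adjustment for markedly imbalanced covariates to secondary analyses. Transformation applies to continuous outcomes such as measured blood loss, change in haemoglobin and haematocrit, and length of stay.

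The open choices therefore lie mainly outside the primary comparison. No sample size or power figure changes.

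**The case against.** The strongest reply is that this is a condensed article. Code-break procedures are usually set out in the full protocol, which may already separate the two tasks. That lowers confidence that the blind would fail in practice. It does not remove the conflict, because the article is not silent here: it assigns both tasks to the same role.

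A second reply is that the harm is small. This largely stands. The primary outcomes and their models leave the analyst little room, and the haemorrhage outcome is calculated from haematocrit against a fixed threshold.

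A third is that few events may occur. Entry is limited to healthy women with singleton pregnancies, and several groups at raised risk of bleeding are excluded. This is why the calculation starts as low as 0.05%. Even there, at least one event is more likely than not.

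A reader might infer more than the text supports:

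- *That the blinded analysis cannot hold, or that the first event necessarily decodes the whole dataset.* Either would need all three conditions in the working to be met, and the article settles none of them.
- *That the disclosed cases would mostly be severe bleeds.* The list names possible consequences of haemorrhage together with any further surgery, intensive care admission for any cause and suspected drug reactions. A loss of 1000 ml does not by itself trigger a form.
- *That the list of SUSARs must be redefined.* Its wording could be clearer, but that is a separate question. Separating the two roles resolves this conflict.

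**Conclusion.** The inconsistency is real. The trial statistician is to analyse blinded and is also to unblind each SUSAR, and the article names no one to separate those tasks. The blinded analysis is a stated property that the procedure does not secure.

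On assumed event rates of 0.05% to 1%, about 1 to 21 allocations would be disclosed to the analyst, with a 65% to more than 99.9% chance of at least one. Actual loss of the blind further assumes constant group codes and linkage to the record.

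The documents do not support a claim that the primary comparisons would be biased. The exposure is mainly in covariate choice for secondary analyses and transformation of continuous outcomes, and any bias is likely to be modest. The point merits correction because the remedy is simple and protects what the trial says it will do.

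**What to change.** 1. In Safety considerations, assign the SUSAR code-break to someone who does not analyse the data. Staff of the unit hosting the web randomisation system are an obvious choice, provided they are not the trial statistician. The article does not say where that statistician works, so this needs checking.
2. Release the allocation only to the DMEC chair and those who must be informed. The trial statistician should not receive it before the analysis is complete.
3. Reconcile the blinding statements in Exclusion criteria, Statistical analysis and Safety considerations, so that each names the same unblinded people. While doing so, state whether the researcher who analyses blinded is a different person from the research fellow or midwife who prepares the infusion; the article does not say.

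The cost is a small change of recipient in the safety procedure. Outcomes, sample size and patient care are unaffected. Whether extra staff time is needed depends on who can hold the codes independently of the analysis.
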